## Abstract

**Background:**

In order to improve lung cancer survival in the UK, a greater proportion of resectable cancers must be diagnosed. It is likely that resectability rates would be increased by more timely diagnosis. Aside from screening, the only way of achieving this is to reduce the time to diagnosis in symptomatic cancers. Currently, lung cancers are mainly diagnosed by general practitioners (GPs) using the National Institute for Health and Clinical Excellence (NICE) guidelines for urgent referral for chest X-ray, which recommend urgent imaging or referral for patients who have one of a number of chest symptoms for more than 3 weeks. We are proposing to expand this recommendation to include one of a number of chest symptoms of any duration in higher-risk patients.

**Methods/Design:**

We intend to conduct a trial of imaging in these higher-risk patients and compare it with NICE guidelines to see if imaging improves stage at diagnosis and resection rates. This trial would have to be large (and consequently resource-intensive) because most of these patients will not have lung cancer, making optimal design crucial. We are therefore conducting a pilot trial that will ascertain the feasibility of running a full trial and provide key information that will be required in order to design the full trial.

**Discussion:**

This trial will assess the feasibility and inform the design of a large, UK-wide, clinical trial of a change to the NICE guidelines for urgent referral for chest X-ray for suspected lung cancer. It utilizes a combination of workshop, health economic, quality of life, qualitative, and quantitative methods in order to fully assess feasibility.

**Trial registration:**

Clinicaltrials.gov NCT01344005

## Background

In 2010, lung cancer caused over 34,800 deaths in the UK, accounting for 7% of all deaths and 22% of all deaths from cancer [1,2]. Five-year survival in the UK is just over 5%, compared with 13% in the USA and similar proportions for several other EU countries [3]. Compared with other countries, patients in the UK have more advanced stage at presentation and a lower rate of lung cancer resections (10%) [3-7]. It has been estimated that 5,000 to 10,000 lives are lost annually in the UK because of probable later diagnosis of cancer [8-10].

Most commonly, lung cancer is diagnosed in the UK following symptomatic presentation to primary care [11]. NICE guidelines have identified the symptoms that should trigger referral for a chest X-ray [12], and suspicious chest X-rays should then be urgently referred to secondary care [11]. The guidelines are currently being updated.

Many patients have had symptoms for a year or more prior to diagnosis [13,14]. Most of the overall time to diagnosis is accounted for by patient or primary care delay, with referral and secondary care delays accounting for relatively less time [15], raising the hypothesis that management of symptoms by GPs, before ordering an X-ray, may delay the diagnosis [16]. A previous study identified a range of factors that delayed GP referral of patients for a chest X-ray including: symptom experience, lack of knowledge, fear, cultural factors, non-standard patterns of healthcare utilization, underlying stoical attitudes, and blame and stigma because of smoking [17]. In the UK, only 23% of diagnoses are made through urgent referrals based on NICE guidelines [18], and patients who are diagnosed following an urgent referral have more advanced TNM (tumor, node, metastasis) stage compared with patients diagnosed through other routes [19], suggesting that the guidance currently identifies those with more advanced disease. The effect of a more or less timely diagnosis is unproven in lung cancer, although there are good arguments to suggest benefit [20].

Several studies of screening with plain X-ray and sputum cytology were undertaken in the 1970s and 1980s. Although none found a mortality benefit [21-23], they all had methodological weaknesses, with the controls receiving some screening, and small sample sizes resulting in inadequate power. However, further information on the value of plain X-ray has recently been provided by the large PLCO (Prostate, Lung, Colorectal and Ovarian Cancer Screening) Trial [24], which assessed the effects of annual screening with modern chest radiography for 4 years in 77,445 subjects compared with 77,456 controls who received usual care. Although screening detected more cancers and more early-stage cancers, there was no evidence of genuine benefit, with no reduction in mortality over 13 years, either in the screened group as a whole, or in a high-risk subgroup (based on the National Lung Screening Trial (NLST) trial inclusion criteria, see below).

The advent of low-dose computed tomography (CT) provided a new tool for screening. In 2011, the landmark American NLST reported the effect of screening for 3 years of current or former smokers aged 55 to 74 with a smoking history of at least 30 pack-years: there was a 20% reduction in mortality from lung cancer and a 6% decrease in all-cause mortality [25]. However, there were serious costs incurred. Suspicious nodules requiring further evaluation were found in 20% of the participants, more than 90% of whom did not have lung cancer. Over-diagnosis, meaning the identification of indolent cancers that would never have become clinically apparent, was estimated to apply to about 25% of the cancers found [26]. It has been estimated that to implement this program nationwide using the NLST inclusion and exclusion criteria would cost $2 billion per annum in CT scan costs alone [27]. When added to the complexities of recruitment of a population that is likely to be hard to reach, and a complex interaction with smoking cessation [28], it is unsurprising that widespread uptake of screening based on this protocol has not occurred.

The largest European low-dose CT screening study, the Nederlands-Leuvens Longkanker Screenings Onderzoek (NELSON) trial, used a longer screening interval than the NSLT and a volumetric method of assessing nodules. Although it has reported a favorable cancer-stage distribution at diagnosis [29], determination of a genuine stage shift at detection, from advanced stage to early stage, will require comparison with the control group. This has not yet been reported, and the size of any benefit resulting from this method remains to be determined.

On the current evidence, we believe that the current best hope for improving outcomes in lung cancer remains with earlier recognition of symptomatic disease at presentation to primary care, and this is most readily done with a chest X-ray. This is because patients who are both high risk and symptomatic have a higher risk of lung cancer than those high-risk patients included in the aforementioned screening studies. A systematic review of interventions to reduce patient and practitioner delay in cancers did not identify any studies relating to lung cancer [30]. A systematic review of interventions to reduce primary care delay in cancer referral did not find any studies that reported a direct effect on reducing delay, or any studies in lung cancer [30].

### The intervention

We propose to lower the threshold (see Figure 1) for a chest X-ray for potential lung cancer symptoms in high-risk patients (that is, the new diagnostic strategy, termed ‘extra-NICE’). This will be compared with current NICE guidance (‘NICE’). Extra-NICE recommends a chest X-ray if one has not been obtained within the previous 3 months, the patient is aged over 60 years, and is a smoker or ex-smoker with 10 or more pack-years of smoking and with: a new or altered cough of any duration reported to primary care, and/or increased breathlessness or wheezing (whether or not associated with purulent sputum).

**Figure 1 F1:**
[figure not shown]
Thresholds for referral for chest X-ray.

Although tumor doubling time is variable, we hypothesize that if tumors are identified earlier, it may be possible to achieve a stage shift, which may translate into higher rates of resections and other radical treatments and an overall improvement in lung cancer survival.

### Main research question

Ultimately, we want to conduct a randomized trial to determine whether or not our extra-NICE guidelines improve lung cancer survival, using resection rates and survival as outcome measures. Using resection rate, which is well correlated with survival, as the main end point of a full trial, and looking for an improvement from 10% to 15%, we would require approximately 1,900 lung cancers, necessitating a UK-wide, expensive trial. Using survival as the main endpoint would require even more cancers. This pilot trial will provide information that will inform the planning of the full trial.

This study fulfills the NETSCC (National Institute for Health Research Trials and Studies Coordinating Centre) definition of both a feasibility and pilot study because it assesses how well the components of the full trial will work together, key parameters that will be required to plan the full trial, and whether or not it is realistically achievable [31].

#### **
*Clinical information*
**

The basic clinical information required is as follows: the prevalence of ‘extra-NICE’ symptoms in patients consulting in UK general practice, the proportion of those who agree to participate, and the proportion of those who are diagnosed with lung cancer.

Of those patients diagnosed with lung cancer, we then require: stage at diagnosis, performance status, and the proportion of patients receiving radical treatments.

#### **
*Process information*
**

The process information required is: the feasibility of primary care recruitment and randomization of patients to a chest X-ray, or not; the best sources of routine data for capturing lung cancers; the best way to train GPs to identify and recruit eligible patients into the trial; the most effective method of presenting the trial (and randomization) to patients; barriers to recruitment and how can we overcome them; and the best measures of resource use and health-related quality of life measures to facilitate health economic analysis of the cost-effectiveness of the extra-NICE protocol.

## Methods/design

### Study design

Ethics approval for the design described here was received from the North Wales Research Ethics Committee (Reference: 11/WA/0222) and is in compliance with the Helsinki Declaration.

The study will have two elements: a Working Group and a pilot trial (see Figure 2) with qualitative and health economic components.

**Figure 2 F2:**
[figure not shown]
Trial schema.

The Working Group of patients and GPs will be convened to establish: the best way to train clinicians to identify and recruit eligible patients into the trial; and the most effective method of presenting the trial (and randomization) to patients (including review of Patient Information Sheet and Informed Consent form).

The chief investigator (CI) will facilitate the Working Group, which will consist of two patient representatives, two non-academic GPs, two nurse practitioners, research network representatives, the trial manager, and a qualitative researcher. Proceedings will be collated in a report highlighting key points to take forward.

We will survey all GPs in South-East Wales to assess the level of interest in the proposed full trial. For the pilot trial, we will select approximately 20 general practices in south-east Wales, and a small number from north Wales and south Yorkshire. GPs at these practices will be trained to recruit patients who fulfill the requirements for extra-NICE (but who do not meet the NICE threshold for referral). Patients willing to participate will be individually randomized 1:1 to one of two arms. Arm A will be the NICE guidance arm; the patient should be treated according to current NICE guidance. Arm B will use the extra-NICE protocol; that is, urgent referral for chest X-ray: the GP orders an urgent chest X-ray through the usual local process.

### Participant eligibility

Eligible patients will be identified within general practices, either during consultations, in chronic obstructive pulmonary disease (COPD) clinics or by retrospective searches of the records of the previous week’s consultations. To be eligible to be included in the trial the patient must meet all of the following criteria: 1) age over 60 years, 2) smoker or ex-smoker (any duration) with 10 or more pack-years of smoking (assessed using http://smokingpackyears.com/. or by dividing the number of cigarettes smoked per day by 20 and multiplying by the number of years smoked), and 3) has given written informed consent; and at least one of the following criteria: 1) a new or altered cough of any duration reported to primary care or 2) increased breathlessness or wheezing (whether or not associated with purulent sputum).

None of the following categories of patients can be included in the trial: 1) patients who qualify for urgent referral for chest X-ray under NICE guidelines that is, hemoptysis, or any of the following unexplained or persistent (that is, lasting more than 3 weeks) symptoms or signs: cough, chest/shoulder pain, dyspnea, weight loss, chest signs, hoarseness, finger clubbing, features suggestive of metastasis from a lung cancer (for example, in brain, bone, liver or skin), or cervical/supraclavicular lymphadenopathy; 2) patients who have had a chest X-ray or CT scan of the chest in the previous 3 months; 3) patients who need a chest X-ray within the following 3 weeks for reasons other than those listed above; or 4) patients previously diagnosed with cancer who have a life expectancy of less than 1 year.

### Sample size considerations

#### **
*Estimating the prevalence of extra-NICE symptoms in patients consulting UK general practices*
**

We have modeled the study using the CAPER (Cancer Prediction in Exeter) lung database [12,15], which contains all primary care consultations, symptoms, and investigations in the 2 years before diagnosis for a 5-year cohort of 247 lung cancer cases, to estimate the potential benefit of expanded chest X-ray use. Smokers aged over 60 years make up 3.2% of the UK population, and we estimate that in a 1-year period, 24% of these would present with extra-NICE symptoms only; that is, 0.768% (or 42 per year in an average practice of 5,500 patients). Hence, if we were to recruit 26 practices (each with a patient population of 5,500) and recruited patients over an average of 6 months (a 12 month recruitment period with practices opening at different points throughout that period), we could get an estimate of this with confidence intervals of 0.70 to 0.83% from a patient-year population of 71,500 (26 × 5,500 × 0.5).

#### **
*Estimating the proportion of those with extra-NICE symptoms who will agree to participate*
**

If we were to find a prevalence of extra-NICE symptoms of 0.768% per year then, from the above, we might find 550 patients eligible for the study. Studies conducted at the Wales Cancer Trials Unit have found a 70% consent rate of eligible patients into trials. We could get an estimate of this with confidence intervals of 70 to 74% in this study.

#### **
*Estimating the proportion of those who agree to participate and who are diagnosed with lung cancer*
**

If 386 (70%) eligible patients consented to participate in the trial, then we could get 95% confidence intervals of 0.9 to 3.9% around an estimate of 2.4% (from CAPER lung database) of those who will be diagnosed with lung cancer.

It was decided to try to open all practices to recruitment for at least 12 months during the running of the trial, so as to avoid any selection bias caused by symptom seasonality.

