### Outcome measures and statistical analysis

The primary analysis will be intention to treat.

#### **
*Primary outcome measures*
**

The primary outcome measures are as follows.

• The prevalence of extra-NICE symptoms in patients consulting a UK general practice. Participating practices will be asked to log a count of all eligible patients. The prevalence will be calculated as the total number of eligible patients logged by the participating practices divided by the total number of patients on their lists.

• The proportion of those who agree to participate. This will be known from trial recruitment, and calculated as the total number of patients recruited by the participating practices divided by the total number of eligible patients logged by them.

• The proportion of those that are diagnosed with lung cancer. This will be obtained from the UK National Lung Cancer Audit Database (LUCADA; available from the NHS Information Centre) and the general practices. It will be calculated as the total number of participating patients found to have lung cancer divided by the total number of patients recruited. A statistical comparison of the proportion in each arm will be made.

#### **
*Secondary outcome measures*
**

We will also assess the following secondary outcome measures

• Of those patients diagnosed with lung cancer, we will assess stage at diagnosis, performance status, and the proportion of patients receiving radical treatments. This will be obtained from LUCADA and the general practices, and proportions will be presented overall and by trial arm.

• Anxiety/depression that may be caused by unnecessary or no chest X-rays. This will be measured using the Hospital Anxiety and Depression Scale (HADS) [32] and informed by the qualitative interviews. This will be presented overall and by trial arm.

• Assessment of false-positive (suspicion of cancer on X-ray but no subsequent cancer diagnosis within 6 months) and false-negative (no suspicion of cancer on the X-ray but diagnosis of lung cancer within 6 months) rates for the chest X-rays. This will be obtained from LUCADA and the general practices, and proportions will be presented overall and by trial arm.

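### The planned 0.70–0.83% interval for prevalence assumes independence across about 26 practices, so it is too narrow if practices differ

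*Protocol article*

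**What the plan says.** The protocol article (Sample size considerations) expects a yearly prevalence of 0.768%, being 24% of the 3.2% of the population who are smokers over 60. It supposes 26 practices with lists of 5,500, open to recruitment for half a year on average, and concludes that "we could get an estimate of this with confidence intervals of 0.70 to 0.83% from a patient-year population of 71,500". No design effect, intracluster correlation (ICC) or between-practice variance is mentioned there. The section closes with a later decision to try to keep every practice open for at least 12 months; the interval was not restated for it.

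Under Study design, about 20 practices are to be selected in south-east Wales, plus a few from two other areas. Under Outcome measures and statistical analysis, prevalence is a primary outcome, and its data arise practice by practice: "Participating practices will be asked to log a count of all eligible patients". Those counts are summed and divided by the summed practice lists. Consent, also a primary outcome, is the "total number of patients recruited by the participating practices divided by the total number of eligible patients logged by them". Neither definition names a method for the confidence interval.

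The article mentions clustering only in the Discussion, as a reason against randomizing by practice.

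**The concern.** The practice is both the unit selected and the unit that measures. Practices can differ in age mix, smoking history and consultation habits. They can also differ in how thoroughly they find and log eligible patients, since Participant eligibility allows identification in consultations, in COPD clinics or by record search. That part of the variance falls with the number of practices, not with the number of patient-years. Individual randomization protects the comparison of arms, but it does nothing for a single-sample quantity such as prevalence.

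The pilot exists to supply planning values for a UK-wide trial. From the article's own figures, 1,900 cancers at 2.4% of participants and 70% consent need 1,900 / (0.024 × 0.70) ≈ 113,000 eligible patients. In practice-years of 5,500 patients:

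- Prevalence of 0.70–0.83% implies about 2,480 to 2,940 practice-years.
- Prevalence of 0.65–0.88% (the interval for an assumed CV of 30%) implies about 2,340 to 3,160, a span nearly twice as wide.

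**Working it through.** **Inputs from the article.** p = 0.032 × 0.24 = 0.00768; k = 26 practices; n = 26 × 5,500 × 0.5 = 71,500 patient-years, or 2,750 per practice. For consent: 70% of the 550 eligible patients expected, about 21 per practice. The 95% level is written only for the cancer interval and is assumed for the other two.

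**Reproducing the stated interval.** p ± 1.96 × √(p(1−p)/n) = 0.00768 ± 1.96 × √(0.00768 × 0.99232 / 71,500), which is 0.704–0.832% and rounds to the printed 0.70–0.83%. A Poisson interval on the same total agrees (0.704–0.832%). A Wilson interval (0.707–0.835%), a 90% level (0.714–0.822%) and n = 143,000 (0.723–0.813%) do not round to the printed pair. Both matching methods treat the patient-years as independent.

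**Allowing for practices.** Take equal practice sizes and let CV be the between-practice coefficient of variation of the logged rate:

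Var = p(1−p)/n + (CV × p)²/k, with t on 25 df (2.06).

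Example, CV 30% and n = 71,500: the first term is 1.066 × 10⁻⁷ and the second is (0.3 × 0.00768)²/26 = 2.042 × 10⁻⁷. The sum is 3.108 × 10⁻⁷, the standard error 0.0557% and the half-width 0.115%. The CVs below are assumptions.

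| Assumed CV | Design effect at 71,500 | Interval at 71,500 | Interval at 143,000 (12 months) |
|---|---|---|---|
| 10% | 1.2 | 0.69–0.84% | 0.71–0.82% |
| 20% | 1.85 | 0.68–0.86% | 0.69–0.85% |
| 30% | 2.9 | 0.65–0.88% | 0.66–0.87% |
| 50% | 6.3 | 0.60–0.94% | 0.61–0.93% |

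Doubling the opening time halves only the first variance term. Setting the 143,000 half-width equal to the printed one (1.96 × 0.0326% = 0.064%) gives a required variance of (0.00064/2.06)² ≈ 9.65 × 10⁻⁸. Subtracting the binomial part, 5.33 × 10⁻⁸, leaves 4.32 × 10⁻⁸ for practices. Hence CV = √(26 × 4.32 × 10⁻⁸)/0.00768 ≈ 14%. Above that, even 12 months in all 26 practices does not achieve the printed precision.

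**Consent.** Under independence, 0.70 ± 1.96 × √(0.21/550) = 66.2–73.8%. With design effect 1 + (550/26 − 1) × ICC:

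- ICC 0.01 (assumed): design effect 1.20, interval 65.8–74.2%.
- ICC 0.05 (assumed): design effect 2.01, interval 64.6–75.4%.

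Clustering therefore adds about 0.4 to 1.6 percentage points per side. The printed interval of 70 to 74% fails even under independence, because its lower limit equals the point estimate.

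**The case against.** Several points on the other side carry weight.

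- **The size is assumed.** Nothing in the article fixes the between-practice variation. At a CV of 10% the interval barely moves, and if 12 months of opening is achieved as well, the result (0.71–0.82%) lies inside the printed one. This stands: no single restated interval can be presented as the right one.
- **The analysis method is not stated.** A reader might infer that the trial will discard between-practice variance in its analysis. The article does not support that. It gives only pooled point estimates and names no interval method. Each practice keeps its own screening log, so the variance can be estimated, and a statistical analysis plan that is not shown may do so. But a later analysis plan would not correct the planning figure as printed.
- **Consent.** A reader might also infer that the consent interval is too narrow because of clustering. Its visible narrowness comes from the lower limit, which is wrong before any clustering is considered.
- **Consequence.** The article ties no progression rule or sample size to this interval, and the cancer proportion (0.9–3.9%) is a much larger planning uncertainty. Both are true, and they limit the weight of the point. Prevalence is nonetheless a primary outcome.
- **Generalization.** Practices are selected, mostly in one region, so even a clustered interval would not capture UK-wide uncertainty. This limits what the fix can deliver, but does not justify assuming no variation between practices.

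**Conclusion.** The point holds for the planning interval for prevalence. The printed 0.70–0.83% carries a design effect of 1 and understates the uncertainty for any positive between-practice variation at the 71,500 patient-years on which it is based. The extent runs from slight (0.69–0.84% at an assumed CV of 10%) to a half-width about 2.6 times the printed one (0.60–0.94% at 50%). If all 26 practices open for 12 months, the extra person-time offsets this up to a CV of about 14% and not beyond. These figures rest on equal practice sizes, 26 practices and assumed CVs. The documents do not show that the printed interval is badly wrong, nor that the analysis will ignore practices. The point is worth correcting because it concerns a primary outcome and costs little.

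**What to change.** 1. Restate the planning interval for prevalence as a range under a declared between-practice CV, labelled as an assumption and including a low value such as 10%. Give it for the person-time now intended.
2. Compute the reported prevalence interval with practice as the cluster: either a ratio estimator with between-practice variance, or a random-practice count model with a person-time offset.
3. Report the between-practice variance from the screening logs. The full trial needs it to choose the number of practices.
4. Correct the lower consent limit as a separate matter (about 66% under independence), and state the small clustering allowance alongside it.

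The cost is some wording and a less favourable stated interval; no extra patients or data are needed.

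### The primary prevalence formula has no time term or fixed window, so the estimate scales with months open; the 12-month opening rule reduces seasonal bias but does not remove it

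*Protocol article*

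**What the plan says.** Protocol article, Sample size considerations: the planning quantity is annual. "Smokers aged over 60 years make up 3.2% of the UK population", and "in a 1-year period, 24% of these would present with extra-NICE symptoms only", which gives 0.768% per year. Precision is worked out on 71,500 patient-years: 26 practices of 5,500 patients, each open for 6 months on average within a 12-month recruitment period, "with practices opening at different points throughout that period".

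The last paragraph of that section records a later decision: "It was decided to try to open all practices to recruitment for at least 12 months during the running of the trial". The reason given is to avoid selection bias from seasonal symptoms. The rule is an aim with a minimum and no maximum.

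Protocol article, Outcome measures and statistical analysis, first primary outcome: "The prevalence will be calculated as the total number of eligible patients logged by the participating practices divided by the total number of patients" on the practice lists. The formula does not mention how long each practice was open, a common logging window or the calendar months covered.

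**The concern.** The two sections define different quantities. The first is a yearly figure with time in the denominator. The second is a cumulative count over list size, which equals the yearly figure only if every practice logs for exactly 12 months. The 12-month decision does not secure that, because it allows longer periods and, being an aim, shorter ones.

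Two errors follow. The estimate rises or falls with months open. In addition, a practice that logs for 15 or 18 months counts some calendar months twice, so the seasonality the rule was meant to deal with is not fully balanced.

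Prevalence is the first primary outcome and, under Main research question, one of the parameters the pilot must supply for planning the full trial. An overstated annual figure would overstate how many eligible patients a practice can be expected to yield per year.

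**Working it through.** **Inputs.** From Sample size considerations: 3.2%, 24%, 5,500 patients per practice, 26 practices, 0.5 years open on average. From the outcome section: logged count divided by list size. Assumed, because the article gives neither: the months open (m), and a seasonal rate of mean × (1 + A cos), with A from 0.2 to 0.5.

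**1. The plan's own figure.**
- 0.032 × 0.24 = 0.00768, and × 5,500 = 42.2 per practice-year (stated: 42).
- 26 × 5,500 × 0.5 = 71,500 patient-years, and × 0.00768 = 549 (stated: 550).
- 0.00768 ± 1.96 × √(0.00768 × 0.99232 / 71,500) gives 0.704 to 0.832% (stated: 0.70 to 0.83%).

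The plan reproduces, and it does so on patient-years. The outcome formula applied to the same scenario gives 549 / (26 × 5,500) = 549 / 143,000 = 0.384%, half the planned figure.

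**2. Effect of open time alone.** With a constant logging rate, the outcome formula returns 0.768% × m/12.

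**3. Seasonal part alone.** Per unit of time, the largest relative error over all opening dates for one practice is A × |sin(πm/12)| / (πm/12).

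| Months open | Formula returns | Error from duration | Largest seasonal error, A = 0.2 | A = 0.5 |
|---|---|---|---|---|
| 6 | 0.384% | −50% | ±12.7% | ±31.8% |
| 9 | 0.576% | −25% | ±6.0% | ±15.0% |
| 12 | 0.768% | 0 | 0 | 0 |
| 15 | 0.960% | +25% | ±3.6% | ±9.0% |
| 18 | 1.152% | +50% | ±4.2% | ±10.6% |
| 24 | 1.536% | +100% | 0 | 0 |

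The 6- and 9-month rows apply only where the 12-month aim is missed.

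**4. Pooled over practices.** Suppose practices open evenly over one year and all close 12 months after the last opens. Mean open time is then 18 months. A season at fraction t of the year gets weight 1 + t, with mean 1.5. The largest seasonal error on a patient-year rate is A × (1/2π) / 1.5 = 0.106A, which is 2.1% at A = 0.2 and 5.3% at A = 0.5. If instead 26 practices are spread evenly over 12 to 18 months with a common close, mean open time is 15 months. Duration then adds 25%, and the largest seasonal error on a patient-year rate is about 3.0% (A = 0.2) to 7.5% (A = 0.5).

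**5. Against sampling error.** The relative half-width is 1.96 × √(0.99232 / (0.00768 × N)):
- N = 71,500: 8.3%.
- N = 143,000 (12 months per practice): 5.9%.
- N = 214,500 (26 × 5,500 × 1.5, the first scenario in step 4): 4.8%.

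The duration error is several times any of these. The seasonal residual is at most of similar size.

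**The case against.** The strongest reply is that the 12-month rule works. A reader might infer that the seasonal bias stays in and that the stated protection fails. The documents do not support that. At the 6-month average first planned, the worst-case single-practice seasonal error is about 13 to 32%; with at least 12 months and opening staggered over a year, the pooled residual is at most 2.1 to 5.3%. Nor are seasons missed by a practice that meets the aim, since 12 months cover them all.

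Second, unequal open periods are inferred. The staggered opening is described for the 6-month scenario, and nothing says that it continues under the later decision or that closure is common. This stands as a limit on the size of the error, but the wording plainly permits periods other than 12 months, and the formula makes no allowance for them.

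Third, the seasonal figures are worst cases over opening date on an assumed amplitude, and the true residual could be near zero. This also stands.

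Fourth, the seasonality sentence can be read as concerning which patients are recruited, not the weighting of the prevalence estimate. That is a fair reading. It weakens the seasonal part but not the conflict over the denominator.

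Fifth, logging windows and standardization are often left to an analysis plan. A stated formula for a primary outcome that disagrees with the stated planning quantity is different: following the article as written gives the wrong annual figure.

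**Conclusion.** The point holds, with the missing time term as the main defect and seasonality as the lesser one. The outcome formula returns the planned annual prevalence only at exactly 12 months open. At 15 months it overstates by 25% and at 18 months by 50%, assuming a constant logging rate. These errors need no assumption about season.

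The seasonal bias is reduced but not removed where open time is not a whole number of years. The pooled residual is at most about 2 to 5% relative for opening staggered over a year with a common close, and about 3 to 7.5% for open periods spread over 12 to 18 months. Both ranges assume a sinusoidal amplitude of 20 to 50%. The residual does not by itself undermine the estimate at the precision the plan accepts (8.3% relative). A patient-year denominator alone would cure the duration error and leave this part in place.

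**What to change.** Define the primary prevalence as eligible patients logged in one complete 12-month window per practice (for example its first 12 months) divided by list size. This returns the annual quantity in the sample size section and weights all seasons equally.

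For a practice open for less than 12 months, use list size × time open as the denominator and standardize by calendar month, using the practices open in each month. Report the all-data patient-year rate as a sensitivity analysis.

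This needs dated log entries and a short change to the outcome definition. Logs beyond each practice's 12 months leave the primary estimate, so its interval widens: for a mean open time of 18 months, the relative half-width goes from 4.8% to 5.9%, which is still tighter than the planned 8.3%. Recruitment can run on past the window unchanged.
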